**3.2 Sample Size Calculation**

The required sample size is calculated using Cochran’s formula for estimating a single population proportion, incorporating finite population correction and a design effect adjustment, as shown in Equation (1). Based on previous studies, we assumed an optimal adherence prevalence of 60%, a two-sided significance level of α = 0.05, and a desired precision (margin of error) of 5%.

A design effect (deff) is included to account for potential clustering introduced by the recruitment workflow, since participants will be conveniently recruited by the designated recruiters through the same platform channels may share unobserved similarities. Following the standard formula deff = 1 + (m – 1) × ICC, we assumed an average cluster size of approximately 11 participants per recruiter and a small intraclass correlation coefficient (ICC) of 0.01. This yielded deff ≈ 1.1, which is applied as a conservative adjustment [7,8].

In addition, a 15% anticipated loss to follow-up is included. The final minimum required sample size is calculated to be 424 participants using PASS software.

n = deff × [N p̂ q̂] / [(d² / 1.96²)(N – 1) + p̂ q̂] (1)

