**3.8 Statistical Analysis Plan**

All statistical analyses will be pre-specified and conducted according to this plan. Analyses will distinguish between event-driven (ED) and daily PrEP regimen users. Both descriptive and inferential statistics will be used to evaluate adherence and associated factors across baseline, 1-, 3-, and 6-month follow-ups.

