**Regression Analyses**

**Event-driven (ED) users:** Three regression models will be fitted:

- Model 1: A univariable and multivariable generalized linear mixed model (GLMM) with a logit link and random intercept to evaluate factors associated with past three-month adherence using data from baseline, 3-month, and 6-month visits. In the multivariable GLMM, all the exposure variables of interest will be involved.
- Model 2: A univariable and multivariable GLMM with the same structure to evaluate factors associated with past one-month adherence using data from baseline and all follow-up visits.
- Model 3: A logistic regression model for consistent adherence, defined using data from the 3- and 6-month follow-ups, with baseline socio-demographics and averaged time-varying covariates included as independent variables.

**Daily users:** Regression analysis is planned only for past one-month adherence (Model 2), using a GLMM with the same structure as for ED users.

All models will include fixed effects for exposure variables of interest. Univariable GLMMs will be fitted first to estimate crude odds ratios (ORs) and 95% confidence intervals (CIs) for each covariate. Multivariable GLMMs will then be fitted including all pre-specified, theory-driven covariates—regardless of their univariable associations—to estimate independent effects while adjusting for potential confounding.

Missing data will be handled under a complete case framework. Specifically, missing data are expected to arise primarily from loss to follow-up. No imputation will be performed. GLMM models inherently allow for unbalanced data across repeated measures, and participants with incomplete follow-up will contribute all available observations. Attrition patterns will be described in supplementary analyses.

All analyses will be performed using R (version 4.4.2). Statistical significance will be defined as a two-sided p-value < 0.05.

1. **Ethics and Confidentiality**

The study protocol will be reviewed and approved by the Institutional Review Board of Tsinghua University. All procedures will be conducted in accordance with the ethical standards of the Declaration of Helsinki and relevant national guidelines.

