Informed consent will be obtained electronically from all participants prior to enrollment. Consent is obtained through a two-step electronic informed consent process conducted anonymously: first, candidates received the e-consent form via WeChat and are enrolled only after replying “agree to participate”; second, the baseline e-questionnaire began with the same consent text and required click-to-consent (“I agree”) before any survey items are displayed. No names or direct identifiers are collected.

Confidentiality of participant data is strictly protected. Each participant is assigned a unique identification key at recruitment, which is used for all subsequent data collection and analysis. No personal identifiers (e.g., name, phone number, address) are collected. Survey data are stored in encrypted files on secure institutional servers with password protection and restricted access. Only authorized research staff have access to the datasets.

Data sharing will follow institutional and journal requirements. De-identified datasets may be made available to qualified researchers upon reasonable request and approval by the corresponding institutional review board.

1. **Anticipated Challenges/Limitations**

- First, the convenience sampling method used in the study (conveniently choosing Bluedhealth as the recruitment channel and conveniently recruited the participants from Bluedhealth PrEP clients) may cause limited generalization ability and selection bias in the study.
- Second, the reliance on self-reported measures to assess PrEP adherence and other factors may introduce recall and social desirability biases. Besides, because participants are repeatedly surveyed at 1, 3, and 6 months, the follow-up process itself may have heightened their awareness of PrEP adherence and modestly influenced self-reported adherence. This monitoring effect could contribute to overestimation of adherence and should be considered when interpreting our results.
- Third, some other factors potentially associated with PrEP adherence (e.g., risk perception, peer support, prior health service use) are not included in the study and need further investigation.

1. **Dissemination Plan**

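### The pooled adherence models name no visit effect, so odds ratios for time-varying exposures can partly reflect a shared time trend; the unmodelled recruiter clustering is a minor matter

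*Protocol*

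**What the plan says.** Section 3.8 is titled as the statistical analysis plan and opens with the statement that "All statistical analyses will be pre-specified and conducted according to this plan". Under Regression Analyses, Model 1 for event-driven users is a "generalized linear mixed model (GLMM) with a logit link and random intercept", fitted to three-month adherence at baseline, 3 and 6 months. Model 2 has the same structure and addresses "past one-month adherence using data from baseline and all follow-up visits", so it pools four waves. The daily-user analysis is Model 2 again. Model 3 differs: "A logistic regression model for consistent adherence, defined using data from the 3- and 6-month follow-ups", with one record per participant.

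On the fixed part, the text says "All models will include fixed effects for exposure variables of interest". Univariable fits come first. Then "Multivariable GLMMs will then be fitted including all pre-specified, theory-driven covariates", a set that the section does not itemise. Neither visit nor recruiter is named, and the level of the random intercept is not given.

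Two other places bear on this. Anticipated Challenges/Limitations says that "the follow-up process itself may have heightened their awareness of PrEP adherence and modestly influenced self-reported adherence" and leaves this to interpretation. Section 3.2 says "A design effect (deff) is included to account for potential clustering introduced by the recruitment workflow", with about 11 participants per recruiter and an intraclass correlation of 0.01.

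**The concern.** Part of the primary objective is to identify factors associated with adherence. Several of these are measured again at each wave. Suppose reported adherence moves between baseline and follow-up, and self-efficacy, for example, moves with it for any reason. A model that pools the waves without a visit term then cannot separate an association with self-efficacy from the common movement over time. A factor that merely changes with visit could be reported as a correlate of adherence. The protocol itself gives one reason why reported adherence might move, and visit is recorded, so the adjustment is available.

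A second, smaller question is whether intervals from models without a recruiter level are too narrow, since the sample size was enlarged for clustering by recruiter.

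**Working it through.** **Inputs from the protocol.** Recruiter cluster size m = 11 and ICC = 0.01 (section 3.2); four waves in Model 2 (Regression Analyses); sample size 424 and assumed adherence 60% (section 3.2). The protocol gives no size for any drift in adherence or in an exposure, so all drift values below are assumptions.

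**1. The protocol's own design effect.** deff = 1 + (m − 1) × ICC = 1 + 10 × 0.01 = 1.10. This reproduces the stated value.

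**2. Visit term.** Random-intercept logistic data were simulated for 424 participants at 4 complete visits. The random-intercept SD was 1.5, the baseline log-odds 0.4 (60% at the average intercept), the true exposure OR 1.00 and the exposure SD about 1, with 60 replicates per setting. Adherence and exposure each stepped between baseline and follow-up. Each data set was fitted with and without a baseline/follow-up term.

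| Adherence step (log-OR) | Exposure shift | OR without visit | OR with visit |
|---|---|---|---|
| 0.25 | 0 | 1.004 | 1.004 |
| 0.5 | 0 | 1.023 | 1.024 |
| 1.0 | 0 | 0.995 | 0.999 |
| 0.25 | 0.2 | 1.022 | 1.007 |
| 0.5 | 0.2 | 1.055 | 1.025 |
| 1.0 | 0.2 | 1.050 | 0.990 |
| 0.25 | 0.5 | 1.055 | 1.018 |
| 0.5 | 0.5 | 1.069 | 0.999 |
| 1.0 | 0.5 | 1.151 | 0.996 |

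Monte Carlo error on each OR is about 0.01 to 0.02. Both models were fitted to the same data, so the difference between the columns is more reliable than either column. With no exposure shift, the visit term changes nothing beyond 0.01. A covariate fixed at baseline had the same OR in both models to within 0.001 in every setting.

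**3. False positives.** A separate simulation used 300 participants, 4 waves, random-intercept SD 1.5, true OR 1.00 and 300 replicates, with drift totals over the study:

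- Adherence +0.9 log-odds, exposure +0.6 SD: OR 1.12 and 25% rejection without visit; 1.01 and 6% with it.
- +0.9 and +0.3 SD: 1.06 and 9%; 0.99 and 5%.
- +0.5 and +0.3 SD: 1.04 and 6%; 1.01 and 3%.
- +0.3 and +0.3 SD: 1.03 and 3%; 1.01 and 3%.

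**4. Recruiter level.** For a regression coefficient, the standard error inflates by about √(1 + (m − 1) × ICC × ρx), where ρx is the covariate's own recruiter-level ICC. The actual coverage of a nominal 95% interval is 2Φ(1.96 / inflation) − 1. At m = 11 and ICC = 0.01:

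- ρx = 1 (covariate constant within recruiter): √1.10 = 1.049, coverage 93.8%.
- ρx = 0.1: √1.01 = 1.005, coverage 94.9%.
- ρx = 0.01: √1.001 = 1.0005, coverage 95.0%.

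If the ICC were 0.05 (an assumption), the worst case would be √1.5 = 1.22, coverage 89.1%.

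**The case against.** The strongest reply is that silence is not exclusion. The protocol says what the models will include, not that they include nothing else. The theory-driven covariates are not listed, and a separate analysis plan may exist. That stands as a caution: the text does not prove that the terms will be absent. It does not dispose of the point, because section 3.8 presents itself as the plan that the analyses follow. The covariate wording could reach visit in the multivariable models only by stretching, and it cannot reach the univariable ones.

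It can also be said that the univariable ORs are openly crude, that prevalence is reported by wave so a trend would be visible, and that the survey effect is already a declared limitation. All true, but none of these removes a shared trend from the multivariable ORs.

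Three stronger readings are tempting and are not supported:

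- A reader might infer that the protocol expects adherence to rise from visit to visit. It says only that surveying may have had a modest influence, and it describes no per-visit trend.
- A reader might take false-positive rates near 25% as the expected consequence. They need adherence to rise by 0.9 on the log-odds scale (conditional OR e^0.9 = 2.46) and the exposure to move 0.6 SD in the same direction. Neither figure comes from the document, and such drift is hard to call modest.
- A reader might apply the full design effect of 1.1 to every standard error. It was derived for a single proportion. The planned exposures are individual characteristics, for which a small ρx is plausible. Event-driven and daily users are modelled separately, so clusters in each model are also smaller than 11. At an assumed average of 6, the worst case is √(1 + 5 × 0.01) = 1.025.

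**Conclusion.** The point holds for the visit effect, in a limited form. Followed as written, Models 1 and 2 for event-driven users and Model 2 for daily users pool waves without adjusting for visit. ORs for exposures that vary over time can then absorb a shared trend. The bias needs drift in both adherence and the exposure. Under the assumed drifts, a true null OR reads about 1.02 to 1.06 for a 0.2 SD shift, and up to about 1.15 for a 0.5 SD shift with strong drift in adherence. It would be wrong to conclude that the ORs in general are confounded by time: fixed socio-demographics are essentially unaffected, and the visit point does not apply to Model 3. These sizes rest on complete follow-up, a random-intercept SD of 1.5 and drift values that the protocol does not supply.

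The recruiter point is minor. Clustering is provided for in the sample size and not carried into any model, Model 3 included. At the protocol's own inputs, standard errors are understated by at most 4.9%, and by about 0.5% or less when ρx is 0.1 or below. That does not support a claim that the intervals are materially too narrow. The visit term is worth requiring because it is nearly free and protects the primary-objective estimates whatever the true drift.

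**What to change.** In Regression Analyses, add visit as a categorical fixed effect to every univariable and multivariable mixed model: baseline, 3 and 6 months in Model 1; baseline, 1, 3 and 6 months in Model 2 for both regimens. State that the random intercept is per participant. Model 3 needs no visit term.

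Optionally, name a sensitivity analysis with recruiter-clustered standard errors or a recruiter random intercept, Model 3 included, or say in one sentence why recruiter is left out. At an ICC of 0.01, the recruiter variance may well be estimated at or near zero.

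The cost is two degrees of freedom in Model 1 and three in Model 2, with no new data from participants. The recruiter analysis only requires that the recruiter be kept with each participant's key. The visit term does not correct any overestimation of adherence prevalence caused by repeated surveying, so that limitation should stay.

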**Primary Outcome**

The primary outcome of this study is PrEP adherence, assessed separately for daily and event-driven (ED) regimen users at each follow-up visit (1, 3, and 6 months after baseline).

- **ED users:** Adherence to ED regimen is assessed by four items. First, the participants are asked whether they had engaged in sexual activity in the past one and three months, respectively (the 1-month follow-up survey only asked this question for the past one month). Those who answer “no” or reported to have never initiated PrEP in a previous question were treated as missing data for PrEP adherence. Those who answer “yes” are then asked if they had taken PrEP for each sexual encounter in the corresponding time period, including those with both primary (e.g., main or long-term partners) and non-primary (e.g., casual or commercial partners) sexual partners (1 = every time, 2 = sometimes, and 3 = never). The participants who choose “every time” or “sometimes” are subsequently asked three adherence questions based on the ‘2-1-1’ dosing guideline: (i) whether (yes or no) they took two pills of PrEP 2 to 24 hours before the sexual activity for each medication (timepoint A); (ii) whether they took one pill 24 hours after the first dose for each medication (timepoint B); and (iii) whether they took another pill 48 hours after the first dose for each medication (timepoint C). The participants who reported to take PrEP for each sexual encounter and chose “yes” to all three adherence questions are classified as “being adherent,” otherwise, they would be classified as “non-adherent.” Lastly, three binary outcome variables are constructed: past 1-month adherence based on baseline and all follow-up data, past 3-month adherence based on baseline and 3- and 6-months follow-up data, and consistent adherence based on 3- and 6-months follow-up data (defined as having optimal past 3-month adherence at both 3- and 6-month follow-up surveys).
- **Daily users:** Adherence to daily PrEP regimen is assessed with a single item: “In the past month, have you ever failed to take PrEP on time and in a correct dosage? (yes/no).” Participants who answer “no” are classified as “adherent,” and those who chose “yes” are categorized as “non-adherent”

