**3.7 Data Management and Quality Control**

Survey responses are automatically recorded on the Wenjuanxing platform and exported as encrypted files. All datasets are stored on password-protected institutional servers, accessible only to authorized study staff. Each participant is assigned a unique identifier at recruitment, which is used throughout all surveys to ensure anonymity. No personal identifiers are collected or stored.

To ensure data quality, each submission is reviewed for completeness, internal logic consistency, and reasonable completion time. Submissions failing these checks are excluded from analysis and do not qualify for incentives. Logic constraints are built into the questionnaire to minimize careless or contradictory responses.

During data management, double validation procedures are applied at the time of dataset export and cleaning. Backup copies are securely maintained, and audit trails are preserved to document data handling. All analytic datasets used for statistical analyses will be fully anonymized.

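### Follow-up adherence prevalence is estimated from responders only, with no check on dropout related to adherence; response-weighted estimates with bounds would be a cheap improvement

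*Protocol*

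**What the plan says.** Section 3.8 is headed as the statistical analysis plan. Under Descriptive Analyses it plans adherence prevalence at each wave, separately for event-driven (ED) and daily users, and names no adjustment for non-response. Under Regression Analyses it fixes the missing-data approach: "Missing data will be handled under a complete case framework. Specifically, missing data are expected to arise primarily from loss to follow-up". It adds "No imputation will be performed", and then "GLMM models inherently allow for unbalanced data across repeated measures, and participants with incomplete follow-up will contribute all available observations". On dropout itself the only commitment is "Attrition patterns will be described in supplementary analyses".

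Two other sections add to what is not observed. Under Primary Outcome (section 3.6), ED users who had no sex in the recall window, or who never started PrEP, "were treated as missing data for PrEP adherence". In section 3.7, on quality checks, "Submissions failing these checks are excluded from analysis and do not qualify for incentives".

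The same Primary Outcome section defines consistent adherence as optimal past 3-month adherence at both the 3- and 6-month surveys. Model 3 analyses it by logistic regression, with one record per person.

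**The concern.** Evaluating adherence is the first part of the primary objective, and section 3.2 sizes the study to estimate an adherence proportion to within 5 points. A proportion among responders estimates the cohort's adherence only if responding is unrelated to adherence. In this cohort that is open to doubt, because people who stop taking PrEP may also be the ones who stop answering surveys about it.

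The justification given in section 3.8 is that mixed models tolerate unbalanced data. That covers Models 1 and 2. It does not cover a raw wave prevalence, or a raw proportion consistently adherent, because neither comes from a mixed model. The limitations section mentions selection through convenience sampling, recall, social desirability and a monitoring effect, but not differential dropout. A reader of the results would therefore have no means of judging how far the follow-up figures could be off.

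**Working it through.** **Inputs from section 3.2:** adherence p = 0.60, margin d = 0.05, z = 1.96, design effect 1.1, loss L = 0.15, stated sample size 424. **Not in the protocol, so assumed:** the population size N, and r, the ratio of the dropout risk in non-adherent people to that in adherent people. The 15% is not tied to a wave; it is applied here to a single follow-up wave.

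**Step 1, the plan's own figure.** With the finite population correction, n = N·p·q / [(d²/1.96²)(N − 1) + p·q].
- N = 3,000 (assumed from the monthly sales figure in the rationale): 328.5 × 1.1 = 361.4, and 361.4/0.85 = 425.1.
- N = 2,900: 327.3 × 1.1 = 360.0, and 360.0/0.85 = 423.6, which rounds up to 424.

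So 424 reproduces for N a little below 3,000. The 15% enters only as an inflation of the number enrolled. That protects precision but does nothing about bias.

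**Step 2, prevalence among responders.** Dropout among adherent people is dA = L / [p + (1 − p)r], and the observed prevalence is p(1 − dA)/(1 − L).

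| r | dA | Dropout, non-adherent | Observed | Bias (points) |
|---|---|---|---|---|
| 0.5 | 0.1875 | 0.0937 | 0.4875/0.85 = 57.4% | −2.6 |
| 1 | 0.1500 | 0.1500 | 0.5100/0.85 = 60.0% | 0 |
| 1.5 | 0.1250 | 0.1875 | 0.5250/0.85 = 61.8% | +1.8 |
| 2 | 0.1071 | 0.2143 | 0.5357/0.85 = 63.0% | +3.0 |
| 3 | 0.0833 | 0.2500 | 0.5500/0.85 = 64.7% | +4.7 |

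At an assumed loss of 10%, ratios of 0.5, 1.5, 2 and 3 give −1.7, +1.1, +1.9 and +3.0. At an assumed 30% they give −6.4, +4.3, +7.4 and +11.4.

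**Step 3, bounds without a dropout model.** Suppose 60% is observed in the 85% retained. If nobody lost was adherent, the cohort figure is 0.60 × 0.85 = 51%. If everybody lost was adherent, it is 0.51 + 0.15 = 66%. In between, each 10 points by which non-responders differ from responders moves the figure by 0.15 × 10 = 1.5 points.

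**Step 4, how much observed data could remove.** This uses a simulation of one million people with a random intercept of standard deviation 1.5 on the logit scale (assumed), adherence of about 60% at every wave, and 15% dropout before month 3 that depends only on baseline adherence. At ratios of 1.5, 2 and 3 the 3-month prevalence among responders was 60.6%, 60.9% and 61.4% against a true 60.1%. The proportion consistently adherent was 43.5%, 43.9% and 44.4% against a true 42.9%. Weighting on earlier adherence can address bias of this kind. When dropout depended instead on consistent adherence itself, with losses of 16.1%, 16.9% and 17.9%, the proportion was 44.7%, 46.1% and 47.9% against the same 42.9%. Weighting on earlier data cannot fully remove that.

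**Step 5, Model 3 odds ratios.** If dropout depends on the outcome alone, it multiplies everyone's odds of adherence by one constant. At r = 2 that constant is 0.8929/0.7857 = 1.136. The intercept moves and the odds ratios do not. The prevalence does move: 1.5 × 1.136 = 1.704, and 1.704/2.704 = 63.0%, as in Step 2.

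**The case against.** The strongest reply is that the size rests on a dropout ratio found nowhere in the protocol, and that the sign reverses if adherent people leave more often. That is correct, so the point is conditional. The baseline prevalence involves no follow-up loss, and the protocol does commit to describing attrition. A description, however, neither corrects the estimate nor says how far it could be off. Nor is the matter simply left to a later document: section 3.8 already fixes complete case and no imputation.

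A reader might also infer several stronger points that the text does not support.

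- *That the ED missing-value rule inflates adherence.* People with no sex in the window have no event-driven adherence to measure. Leaving them out narrows the population described, and relabelling them changes no estimate. The protocol says that missing data arise primarily, not only, from loss to follow-up, so the rule does not contradict it.
- *That complete case contradicts the use of all available observations.* The same paragraph explains the meaning: nothing is imputed, and participants contribute the visits they have.
- *That Model 3 is valid only if dropout is unrelated to adherence.* Step 5 shows otherwise. Its odds ratios are biased only if dropout depends jointly on outcome and covariates.
- *That sexually inactive daily users are deleted from their model.* The protocol does not show how sexual role and condom use are coded when there was no sex, so this cannot be established.

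**Conclusion.** The concern holds for the raw 1-, 3- and 6-month prevalences and for any reported proportion consistently adherent. It does not extend to the mixed models, which are valid under missing at random if correctly specified. At the protocol's 60% and 15%, assumed dropout ratios of 1.5 to 3 cost about 35% to 94% of the 5-point margin, and that error would not show in the confidence interval. The margin is only a yardstick: it was set for one proportion in the whole sample, and prevalence will be reported by regimen, where sampling error is larger.

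A reader might conclude that the study will overestimate adherence. The documents do not establish that, because they give neither the direction nor the strength of any link between dropout and adherence. What they do show is that the plan offers no way to find out. This is a cheap improvement rather than a flaw that invalidates the study.

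**What to change.** In section 3.8, for each follow-up wave and for the proportion consistently adherent:

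1. Keep the unweighted estimate and show beside it one weighted by the inverse probability of response, modelled on baseline covariates, recruitment round and last observed adherence.
2. Add simple bounds as in Step 3, or a delta analysis in which non-responders' adherence differs from responders' by a stated range. This is needed because weighting corrects only dropout explained by observed data.
3. Count ED users with no sex in the window, or who never started PrEP, separately from non-responders at each wave, so that the weights apply to non-response only.
4. Optionally refit Model 3 with the same weights as a sensitivity analysis.

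The cost is a short paragraph of wording, a little more analysis and slightly wider intervals for the weighted estimates. The variables are already collected, so no new data are needed.
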